# CO-CREATION-HF protocol: clinical trial to evaluate the impact of a comprehensive and hybrid cardiac rehabilitation model on patients with heart failure

**DOI:** 10.3389/fcvm.2024.1427544

**Published:** 2024-11-14

**Keywords:** cardiac rehabilitation, exercise, heart failure, telerehabilitation, adherence, psychosocial support

## Abstract

**Introduction:**

Comprehensive, hybrid cardiac rehabilitation (CR) models have been scantly investigated in heart failure (HF) populations, particularly in low-resource settings. CO-CREATION-HF aims to evaluate the effectiveness of such a model compared to supervised exercise alone.

**Methods and analysis:**

A 2 parallel-arm, multi-center randomized clinical superiority trial will be conducted with blinded outcome assessment. 152 HF patients (NYHA class II or III) will be recruited consecutively, and randomly assigned using permuted blocks; allocation will be concealed. The 12-week intervention will include evaluation, medical and nurse management, aerobic interval training, resistance exercise training, psychosocial support, and education. These will initially be delivered in a center, transitioning to home in 4 stages. Controls will receive similar management, but face-to-face continuous aerobic exercise sessions and resistance exercises. The main outcomes are cardiorespiratory fitness (VO_2_ max), functional capacity (m from 6 MWT), and quality of life (Minnesota Living with Heart Failure Questionnaire). Program adherence and completion, NT-proBNP, functioning, all-cause and HF-specific mortality and hospitalization, muscle strength, adverse events and cost will be secondary outcomes. These will be measured at baseline, end of intervention, and 12-month follow-up. The sample size was calculated considering 90% power, a significance level of 5%, a between-group difference equivalent to 1/2 MET, and a 10% potential loss to follow-up. Intention-to-treat analysis will be considered. Between-group differences will be assessed using Student's *t*-tests or *Z*-tests along with 95% confidence intervals, and the rate ratio will be computed to compare mortality.

**Ethics and dissemination:**

The study protocol and the Informed Consent form were approved by Ethical Committees at the Universidad de La Frontera (No. 081-23) and each center participating. Research findings will be disseminated to the scientific community and will be shared with relevant stakeholder groups and policy-makers. Finally, investigators shall reach HF patients via various dissemination channels such as social media.

**Clinical Trial Registration:**

clinicaltrials.gov, identifier (NCT06313684).

## Introduction

1

Heart failure (HF) is characterized by symptoms and signs such as breathlessness, ankle swelling, and fatigue that result from structural or functional impairment of ventricular filling or ejection of blood (1). HF is a growing global health challenge, with a substantial burden due to low exercise tolerance, poor health-related quality of life (HRQoL), as well as high risk of mortality and hospital admission, which all culminate in high use of healthcare resources and costs (2). Indeed, HF is the leading cause of hospitalizations in people >65 years (3).

Although HF incidence has remained stable or has even declined, prevalence is increasing due to the aging of the population. The age-standardized prevalence of HF varies substantially across regions, ranging from 498 (Southe3ast Asia) to 1,196 (Central Europe) per 100,000, correlating with the sociodemographic development of countries, as it does with the years lived with HF disability. In the Latin American low and middle-income context, high age-standardized rates of prevalent cases are also found, particularly in Central countries in the region, such as Nicaragua with 912.4 and Venezuela with 991 (4).

Several clinical guidelines have been developed to support optimal treatment and monitoring of patients with HF. HF has no definitive cure, and therefore, recommendations are aimed at controlling symptoms, improving functional capacity, optimizing quality of life and prolonging patient survival. Self-management of multiple behaviors is key to preventing acute exacerbations and hospitalizations.

In particular, clinical guidelines internationally recommend exercise or exercise-based cardiac rehabilitation (CR) as a non-pharmacological intervention for HF, but they do so weakly primarily due to the low or moderate certainty of the evidence (1, 5, 6). The Cochrane review of exercise-based CR for HF Patients updated in 2019 (7) which included 44 randomized clinical trials (RCTs), plus additional sequential analysis (8), concluded that compared to no exercise, continuous aerobic exercise appears to have no impact on short-term mortality, probably reduces the risk of hospitalization, and would improve HRQoL. It is important to note that most of the included trials are from “Western” high-resource settings and tested exercise only, with only 3 RCTs in low or middle-income countries and 12 RCTs incorporating other CR components such as education. Comprehensive CR could result in more favorable outcomes, given patients also receive education and psychosocial counseling or support so they understand the importance of self-management via exercise and other health behaviors and can overcome barriers to adherence to these behaviors. Other factors that can lead to disease progression are also addressed in comprehensive CR, such as diet, medication adherence and tobacco cessation where applicable.

The HF-ACTION trial (9) was influential in the Cochrane review because it included more than 1,000 patients per arm, impacting the current guideline recommendation for exercise in patients with HF. Based on this trial—conducted in the United States, Canada, and France– the authors concluded that exercise training was associated with modestly-significant reductions in both all-cause mortality or hospitalization and cardiovascular mortality or HF hospitalization. However, there were some limitations of HF-ACTION, including that it was not pragmatic in its’ approach as patients were provided with special equipment to exercise at home, limiting generalizability especially in low-income settings; as well as the low adherence to the intervention (30%), which is also a problem in routine clinical practice. This latter aspect is fundamental, as patients with HF experience considerable fatigue and breathlessness, resulting in exercise intolerance, so it is necessary to tailor exercise prescriptions individually and incorporate interventions that support adherence. Unfortunately, however, most patients with HF do not even access CR (10), underscoring the challenges in delivering CR for these patients.

Also concerning the issue of the degree of CR impact in HF populations, emerging evidence has supported the benefits of CR of a minimum 3 months (11), as well as with higher-intensity exercise (12), including interval training (13). Indeed, the greater the dose of CR, the lower the mortality, among other benefits (14). However, many trials and real-world CR models often do not offer CR of sufficient “dose”/sessions to realize the significant benefits (15). In low-resource settings, patients receive even fewer CR sessions. Interval training may be of particular benefit in HF because patients can reach higher exercise intensities, optimizing impact of each session attended (16, 17).

An approach to address low adherence for HF is offering home-based delivery (18–20) or hybrid models (21–23) vs. the traditional center-based models. Specifically, hybrid CR, defined as a combination of center-based and home-based, has been shown to improve physical function, exercise capacity and HRQoL in patients with HF when compared with usual care. They have also been shown to be safe in this population (19). However, more studies are needed to clarify if hybrid CR produces superior outcomes than traditional center-based models, and also to better define the role that technology should play in non-supervised CR for HF (22).

In light of the available evidence, where the emphasis has been on conventional exercise (basically continuous, supervised aerobic exercise) with little success (probably due to lack of adherence) and recalling the definition of CR as a multi-component intervention, it is time to investigate a comprehensive HF-tailored CR model pragmatically-delivered for low-resource settings addressing the knowledge gaps identified, to achieve optimal outcomes in this challenging population in great need. Indeed, there have been very few clinical trials evaluating the effectiveness of comprehensive hybrid CR in HF patients, such as the REACH-HF (Rehabilitation EnAblement in CHronic Heart Failure) (23) and TELEREH-HF (The Telerehabilitation in Heart Failure Patients) (24) studies in high-resource settings. Figure 1 shows the state of the art and the knowledge gaps that triggered this proposal.

**Figure 1 F1:**
[figure not shown]
Summary of the scientific novelty of the trial about the heart failure literature.

The CO-CREATION-HF (Comprehensive Hybrid Cardiac Rehabilitation Trial to Assess Impact on Heart Failure Patients) trial aims to evaluate the effectiveness of comprehensive hybrid (including the use of mobile phones) CR compared to a supervised exercise-based intervention alone on maximum cardiorespiratory capacity, functional capacity, and HRQoL. Secondarily, effectiveness for program adherence and completion, pro-B-type natriuretic Peptide (pro-BNP), functioning, mortality and hospital admission, skeletal muscle strength, exercise-related adverse events, and costs will also be compared.

## Methods and analysis

2

### Design

2.1

A pragmatic, multi-center, 2-parallel arm randomized clinical trial with blinded outcome assessment will be conducted. In this study, a hypothesis of superiority is tested (i.e., a comprehensive and hybrid CR program produces better results than a conventional exercise-based supervised program). This trial will be pragmatic in that it examines the outcomes of the experimental intervention compared with a control group under circumstances that closely approximate the real world, in a low-resource setting. Patients will be recruited in 4 health centers in Chile. It is not possible to double-blind in a CR trial, but personnel undertaking outcome assessment will be blinded to group allocation. Finally, the randomization process (concealed allocation 1:1) will allow balancing in both groups of all known and unknown sociodemographic and clinical characteristics that could confound the association between the intervention and results.

The trial protocol is registered in clinicaltrials.gov (number NCT06313684). It will be reported in accordance with the CONSORT statement (25), including the extensions for non-pharmacologic treatment interventions, and pragmatic trials. A diagram of the trial showing activities in detail is presented in Figure 2.

**Figure 2 F2:**
[figure not shown]
Flowchart and timeline for activities in the CO-CREATION-HF trial.

### Study population

2.2

The reference population is chronic HF patients. The accessible population is patients that attend one of the 4 Chilean tertiary hospitals involved in the study: Complejo Hospitalario San José, Hospital Clínico de la Universidad de Chile, Hospital Clínico San Borja Arriarán y Hospital [name] Aravena. The sampling will be non-probabilistic of consecutive cases, with a sample of patients in the above centers meeting specific eligibility criteria presented in Table 1.

**Table 1 T1:** Eligibility criteria for CO-CREATION-HF trial.

Inclusion Criteria	Exclusion criteria
– Adult patients with HF (HFrEF, HFmrEF, and HFpEF) of New York Heart Association functional class II or III (26) – Meets HF diagnostic criteria of Guidelines (1, 5) • HFrEF: Symptoms/signs of HF and ejection fraction ≤ 40%. • HFmrEF: Symptoms/signs of HF and ejection fraction 41%–49%. • HFpEF: Symptoms/signs of HF, ejection fraction ≥ 50% and objective evidence of cardiac structural and/or functional abnormalities consistent with the presence of left ventricular diastolic dysfunction/raised LV filling pressures, including raised natriuretic peptides. – On maximum tolerated medical therapy available according to current guidelines (5, 27, 28) – Deemed by the treating physician as stable for at least 1 month. – Able to attend the health center three times a week for the first month, and twice a week for the 2nd and 3rd months – Owns a mobile phone – Patient consents to participate in the study by signing an informed consent form.	– Chronic kidney disease with glomerular filtration rate < 20 ml/min. – Decompensated thyroid disease. – End-stage liver failure or Child Pugh C. – Cardiac device (implantable defibrillator or cardiac resynchronization) or cardiac surgery (revascularization or valve procedure) in the previous month or planned in the next 3 months. – Patients with dyspnea predominantly of non-cardiac cause (e.g., decompensated COPD). – Atrial fibrillation with a heart rate greater than 90 beats per minute at rest. – Active neoplasm with life expectancy <2 years. – Inclusion in another interventional study. – Explicit contraindication to performing exercise based on the American College of Sports Medicine guidelines (29). – Comorbidities such as dementia, blindness, deafness, serious mental illness, or frailty (defined as dependent according to EMPAM classification) the precludes the patient from engaging in a CR program. – Musculoskeletal or neurological disease that precludes the patient from performing exercise.

HF, heart failure; HFrEF, heart failure with reduced ejection fraction; HFmrEF, heart failure with mid-ranged ejection fraction; HFpEF, heart failure with preserved ejection fraction; COPD, chronic obstructive pulmonary disease; EMPAM, examen médico preventivo del adulto mayor [preventive health examination of the older adult]; CR, cardiac rehabilitation.

### Sample size

2.3

One hundred and thirty-eight patients (69 per group) are required to have a 90% chance of detecting as significant at the 5% level, a difference in the primary outcome measure of maximum cardiorespiratory capacity (VO_2_ max), assuming 15 ml/Kg/min in the control group and 16.75 ml/Kg/min in the experimental group at intervention end. The VO_2_ max assumed in the control group is that achieved by the experimental group with exercise-based CR in the HF-ACTION trial (9), with a standard deviation of 3.15 calculated with the range rule. The VO_2_ max in the experimental group was assumed with an intermediate minimal important difference of 1/2 MET (1.75 ml/kg/min) (30, 31). If a potential 10% loss of follow-up is added, results in 152 patients (76 per group). Sample sizes were also calculated for the other two primary outcomes, functional capacity, and HRQoL, with fewer patients needed to test the underlying hypothesis.

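### The loss-adjusted sample size should be 154, not 152, and the 90% power rests on an SD of 3.15 whose derivation cannot be checked

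*Protocol article*

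**What the plan says.** The Sample size section states that 138 patients, 69 per group, "are required to have a 90% chance of detecting" a difference in VO2 max at the 5% level, "assuming 15 ml/Kg/min in the control group and 16.75 ml/Kg/min in the experimental group at intervention end". The difference is an "intermediate minimal important difference of 1/2 MET (1.75 ml/kg/min"). The control mean is taken from the exercise arm of a cited large trial, "with a standard deviation of 3.15 calculated with the range rule". The section does not say which interval was used, how wide it was, or what it was divided by. The Introduction says of the same cited trial that "it included more than 1,000 patients per arm".

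For attrition, the section says: "If a potential 10% loss of follow-up is added, results in 152 patients (76 per group").

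The Analysis plan section compares continuous outcomes between groups with Student's t-tests at each follow-up point. Multiple linear regression enters only if baseline characteristics turn out to be imbalanced. Table 4 shows that cardiorespiratory fitness is measured at baseline, at 3 months and at 1 year.

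**The concern.** The SD is the input to which this power calculation is most sensitive, and the section names a shortcut for it. The usual form, range/4, works when the sample minimum and maximum lie about 4 SD apart, which is true of samples of about 25. In a sample of 1,000 they lie about 6.5 SD apart, so range/4 does not recover the SD of a source of the size that the Introduction gives. Without the interval and the divisor, a reader cannot tell whether 3.15 is too large, too small or about right. The planned primary test is unadjusted, so the full between-patient SD determines its power.

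The loss allowance is a separate and smaller matter. Multiplying by 1.10 does not leave the required number after 10% are lost.

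**Working it through.** **Inputs from the Sample size and Design sections.** Difference 16.75 − 15 = 1.75 ml/kg/min; SD 3.15; 5% level; 90% power; "concealed allocation 1:1". Sidedness is not stated. A two-sided test reproduces the plan's figure, while a one-sided test would need only 56 per group.

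**Reproducing the plan's number.** n per group = 2 × [(1.96 + 1.2816) × 3.15 / 1.75]² = 68.1, rounded up to 69, or 138 in total. The t-test version needs 69.06 and has power 0.8997 at 69. The plan's 138 is therefore right for its inputs.

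**Loss to follow-up.**
- Plan: 138 × 1.10 = 151.8, rounded to 152.
- Completers if 10% of 152 are lost: 152 × 0.90 = 136.8, or 68.4 per group, short of 138.
- Correct inflation: 138 / 0.90 = 153.3, rounded up to 154 (77 per group).
- Loss that 152 can absorb: 1 − 138/152 = 9.2%.
- Power with 68.4 per group at SD 3.15: 0.897 (t-test) or 0.901 (normal approximation).

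**What 3.15 could mean.** The simulated expected range of a normal sample is 3.93 SD at n = 25 and 6.49 SD at n = 1,000. Each reading below is an assumption, because the document gives neither interval nor divisor. Power is for 69 per group.

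| Assumed origin of 3.15 | Interval width | Implied SD | Power |
|---|---|---|---|
| Minimum-to-maximum range / 4 | 12.6 | 12.6/6.49 = 1.94 | above 99% |
| Minimum-to-maximum range / 6 | 18.9 | 18.9/6.49 = 2.91 | 94% |
| Central 95% interval / 4 | 12.6 | 12.6/3.92 = 3.21 | 89% |
| Interquartile width / 2 | 6.3 | 6.3/1.35 = 4.67 | 59% |

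**Sensitivity to the SD, unadjusted t-test, 69 per group.** 3.15 gives 90%; 3.5 gives 83%; 4.0 gives 72%; 5.0 gives 53%.

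**Effect of adjusting for baseline VO2 max.** Residual SD = SD × √(1 − r²), where r is the correlation between baseline and 3-month values. The document gives no r. With r = 0.7 and SD 4.67, the residual SD is 4.67 × √0.51 = 3.34, and power rises from 59% to about 86%. With r = 0.5 it is 4.67 × √0.75 = 4.04, and power is about 71%.

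**The case against.** The strongest defence is that nothing here shows the trial to be underpowered. The 138 follows from the stated inputs. If 3.15 came from a true minimum-to-maximum range divided by 4, the size of the source means that the SD was overstated and the trial is conservative. A divisor of 6 is close to the expected 6.5 SD and leaves power at about 94%. Only a partial interval, such as an interquartile width, gives a materially larger SD, and the article never mentions one. All of this stands, and it limits the point to saying that the 90% cannot be verified.

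A reader might go further and infer that, at an SD of 4 to 5, a null result could not rule out the 1.75 difference. That does not follow. At SD 5 the standard error is 5 × √(2/69) = 0.851 and the 95% half-width about 1.68; at SD 4.67 the half-width is about 1.57. An estimate near zero would still exclude 1.75. Only an estimate leaning towards benefit would fail to do so.

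It is also fair to say that a condensed article may leave the interval to the full protocol. But the article does state how its SD was derived, and it names a rule whose common form does not fit the source it cites.

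Finally, the loss slip is worth two patients and leaves power at about 90%. It is a correction to a figure and does not undermine the power. That regression is already available when imbalance is seen is true, but this makes the choice of analysis depend on the data and does not secure the precision gain in advance.

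**Conclusion.** Two points hold. First, the loss-adjusted total is miscalculated: 154 is the figure that leaves 138 after 10% loss, and 152 tolerates only 9.2%. The effect is small, with power of about 89.7% at 10% loss if the SD is 3.15. Second, the SD behind the 90% cannot be verified, and the direction of any error is unknown. Across the readings tabulated above, power runs from above 99% to 59%. The lower end rests on an interquartile width that the document does not report, so a reader who concluded that the power is overstated would be going beyond the text.

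The exposure is avoidable, because baseline VO2 max is already measured and the plan does not commit to using it. How much adjustment would recover depends on an assumed correlation.

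**What to change.** 1. In the Sample size section, replace the range-rule SD with a reported SD. Failing that, name the interval and convert it properly: interquartile width/1.35, or for a confidence interval of a mean, width × √n/3.92. Then restate the power of the planned 152 at that SD.
2. Either write the loss adjustment as 138/0.90, giving 154, or keep 152 and say that it allows for 9.2% loss.
3. In the Analysis plan section, pre-specify the comparison adjusted for baseline VO2 max as the primary analysis, in place of an unadjusted t-test with regression only when imbalance appears. Give the power on its residual SD, with the assumed correlation stated.

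The cost is a rewritten sample-size paragraph and a changed analysis sentence. No extra enrolment is needed, since option 2 allows 152 to stand, and no new measurement is required. The downside is that the stated power may be slightly less favourable.

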### Recruitment and randomization

2.4

Patients will be invited to participate in one of two ways: at the routine consultation of the HF polyclinic in each hospital, or through a telephone call by the nurse in charge of the HF census operating in two hospitals. All information about the study will be delivered by a nurse, physician or physiotherapist in charge of this task exclusively, and who will be unaware of the randomization sequence. If patients consent to participate in the study, an initial evaluation will be performed to collect baseline sociodemographic as well as clinical characteristics and measures.

Assignment to the experimental or control group will be by permuted blocked randomization and conducted by an independent researcher. Concealment of the assignment will be preserved through the functionality available in REDCap© (32), and will only be known to the therapist who receives the patient in the CR program. The core components for both arms in the study are presented in Table 2.

**Table 2 T2:** Core cardiac rehabilitation components for experimental and control programs.

	Comprehensive hybrid CR	Supervised exercise-based CR
Initial Assessment	Includes all those necessary to prescribe exercise training, as well as dietary and adherence promotion interventions. – Functional capacity with 6 MWT – Assessment of skeletal muscle strength, flexibility, and balance. – Assessment of functioning – Assessment of dietary habits – Assessment of self-efficacy and barriers to CR adherence. – Screening for depression.	Includes all those necessary to plan exercise training, as usual: – Functional capacity with 6 MWT. – Assessment of skeletal muscle strength.
Continuous evaluation:	Evaluations during the course of the program will be carried out to inform the progression through the CR stages, the intensity of training and education needs.	Not applicable.
Medical and nurse clinical management:	Performed following the recommendations in the guideline update of the American and European societies (1, 28). 25	
Exercise	High-intensity interval training prescribed by physical therapist: – According to an adapted Wisloff protocol (33). – Borg scale to monitor intensity (34). – Training 3 times per week. Resistance exercises training: – With TheraBand OMNI-Resistance exercise bands. – Intensity will be based on participant's subjective perception, according to the perceived exertion scale (70%–80% 1 RM) – Frequency at least twice a week.	Moderate-intensity continuous exercise prescribed by physical therapist: – The intensity will be moderate, as tolerated – Borg scale to monitor intensity (34). – Frequency of training of 1 to 3 times per week, until completed 20 sessions in 10–12 weeks. Resistance exercices. – With available materials. – Moderate intensity – 1–2 times a week.
	Exercise volumes (interval plus resistance and continuous plus resistance) shall be equivalent between the experimental and control groups.	
Psychosocial support:	Based on social-cognitive theory (35) and delivered by a trained professional (occupational therapist or nurse), with self-efficacy as a focus, it will include: – Two face-to-face sessions in the first stage of the program: Education, self-monitoring and motivational interview. – One face-to-face session in the second stage of the program: promoting behavior changes by self-control and self-monitoring – Regular communication with patients will be supported by the use of mobile devices during the third and fourth stages of program. – Referral to a specialist will be considered if depression is detected in the screening.	Not applicable
Diet management	– Dietary plan supported by a nutritionist will be made together with the patient.	Not applicable

CR, cardiac rehabilitation; RM, repetition maximum; 6 MWT, 6 min walk test.

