### Control group

2.6

The patients in the control group will receive the conventional center- and exercise-based CR at the participating centers. These programs consist of an initial assessment as well as medical and nurse management. The exercise component will comprise continuous aerobic exercise sessions plus resistance exercises. Continuous moderate exercise sessions will be of 10 min duration at the beginning of the program, and progress to 30 min by the end, as tolerated by each patient; the patient may rest between the exercises to complete the maximum tolerable exercise time. The resistance exercise training will include polyarticular and monoarticular movements against mechanical resistance or free weight. The intensity of this training will be moderate as per the Borg perceived exertion scale (34), specifically as “fairly light to somewhat hard” (score 12–13) or 50%–60% of the estimation of 1 RM. Additionally, a safety range will be set at 40%–60% HRR, which corresponds to moderate intensity. These programs typically last 10–12 weeks (3 months) with 20 supervised exercise sessions.

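### The stated between-group test in this four-center trial is unadjusted, with adjustment only after an observed baseline imbalance; prespecifying center as a fixed effect would be the better primary analysis

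*Protocol article*

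**What the plan says.** - **Setting (section 2.1).** "Patients will be recruited in 4 health centers in Chile". Allocation is 1:1 and concealed, and randomisation "will allow balancing in both groups of all known and unknown sociodemographic and clinical characteristics".
- **Allocation (section 2.4).** "Assignment to the experimental or control group will be by permuted blocked randomization and conducted by an independent researcher", with concealment through REDCap. No stratification factor or block size is given. Section 2.9 makes a local coordinator at each hospital responsible for random assignment, among other tasks. The two statements do not settle whether there is one list or four.
- **Control arm (section 2.6 and Table 2).** Control patients "will receive the conventional center- and exercise-based CR at the participating centers". A common frame is described: "These programs typically last 10–12 weeks (3 months) with 20 supervised exercise sessions", with set intensity ranges. Table 2 leaves the resistance equipment to what is available.
- **Analysis (section 2.8).** Continuous outcomes are compared by Student's t-test at each follow-up point, with confidence intervals for the mean difference. If baseline characteristics turn out to be imbalanced, a multiple linear regression is fitted. No covariate is named for that model, and center appears nowhere in the section.

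**The concern.** Center is a plausible source of outcome variation here: there are four hospitals, and each supplies its own conventional program as the control. An unadjusted t-test leaves any between-center variance in the error term.

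What that costs depends on how the lists were built. With one list across hospitals, the arms can be unevenly split within a center by chance, and the unadjusted estimate carries the resulting noise. With lists stratified by center, that noise has been removed by design, but the t-test still charges for it, so its standard error is too large.

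A model chosen only after an imbalance is seen also makes the primary analysis depend on the data. At stake are precision, agreement between design and analysis, and a primary model that is fixed in advance.

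**Working it through.** **Inputs from section 2.3:** means 15 and 16.75 ml/kg/min (difference 1.75), SD 3.15, 5% level, 90% power, 69 per arm, 152 in total after 10% loss. **Assumed, because the article does not give them:** center sizes, block size, and the share s of VO2 max variance lying between centers (range 0–20%).

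**1. The plan's own figure.** n per arm = 2 × [3.15 × (1.960 + 1.282) / 1.75]² = 68.1, rounded up to 69, so 138 in total. 138 × 1.10 = 151.8, giving 152. The figure reproduces with a two-sided test and does not bear on this point.

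**2. Chance imbalance within centers** (152 patients; blocks of 4 or 6; centers of 38 each or 70/40/25/17).
- *One list:* the arm difference in the worst-balanced center has median 7–8 patients and 95th percentile 13–14. At least one center is split 60:40 or worse in 51–64% of runs.
- *Stratified by center:* median 1–2, 95th percentile 2, and no split of 60:40 or worse.
- Mean bias is about zero under both.

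**3. What that means for the estimate.** With one list, the center-driven part of the treatment difference has SD √s × 3.15 × √(2/76). This is 0.07 at s = 2%, 0.16 at 10% and 0.23 at 20% (ml/kg/min). The full standard error is 3.15 × √(2/76) = 0.51, and the target difference is 1.75. In a single trial, a 24 v 14 split in a center whose mean differs by 2 ml/kg/min (assumed) from otherwise equal centers would move the estimate by (24 − 14)/76 × 2 = 0.26, or 15% of 1.75.

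**4. Size and power of the two analyses** (138 patients, centers of 35/35/34/34, blocks of 4, 6,000 runs per setting):

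| Share s | One list: t-test type I | One list: t-test power | One list: center-model power | Stratified: t-test type I | Stratified: center-model type I |
|---|---|---|---|---|---|
| 0% | 5.0% | 89.9% | 89.3% | 4.7% | 4.8% |
| 2% | 5.2% | 90.2% | 90.3% | 4.6% | 4.8% |
| 5% | 5.2% | 89.6% | 90.4% | 4.5% | 5.0% |
| 10% | 5.1% | 90.2% | 92.3% | 3.9% | 5.0% |
| 20% | 5.3% | 90.3% | 95.0% | 2.5% | 4.4% |

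Monte Carlo standard errors are about √(0.05 × 0.95/6000) = 0.3 points for type I error and √(0.9 × 0.1/6000) = 0.4 points for power. With stratified lists, the center model raises power from 91.3% to 92.6% at s = 10% and from 92.5% to 95.2% at s = 20%.

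**5. Analytic check of the conservatism.** Under stratification the true standard error is about √(1 − s) times the one the t-test uses. Type I error is then about 2Φ(−1.96/√(1 − s)): 4.8% at s = 2%, 3.9% at 10% and 2.8% at 20%. This agrees with the simulation; repeat runs gave 3.9–4.3% at 10% and 2.5–3.0% at 20%.

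**The case against.** The strongest case against is that nothing here is invalid, and much of it stands.

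- **Confounding.** A reader might infer that arm and center are confounded. The article does not support that. Patients are individually randomised 1:1 and no hospital is tied to one arm. Expected bias is zero, and the one-list t-test keeps its 5% level because its standard error already covers chance imbalance by center.
- **Differing control programs.** A reader might take these as a source of confounding. They would make the treatment effect vary by center, which is a matter of heterogeneity and interpretation. Section 2.6 also gives the programs a common frame, which limits the variation.
- **Recruitment routes.** Two hospitals also recruit "through a telephone call by the nurse in charge of the HF census operating in two hospitals", but clinic recruitment runs in every hospital and both routes precede randomisation. They feed both arms alike.
- **Stratification.** A reader might infer that center is not used in allocation. Section 2.4 is silent, and silence in a condensed article is not exclusion; the REDCap lists may already be stratified.
- **Existing safeguard.** Section 2.8 acknowledges chance imbalance and provides for regression. That softens the strong claim in section 2.1. It does not replace a prespecified model, because it is triggered by the data and names no covariate.

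The between-group test itself is not silence. Section 2.8 states it, and a center-adjusted model does as well or better under either allocation scheme unless centers hardly differ.

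**Conclusion.** The point holds as one of efficiency and of matching analysis to design. It is not a threat to validity. With one list, leaving center out costs about 0–2 points of power at a 2–10% between-center share and about 5 points at 20%. With stratified lists, the stated t-test is conservative: about 4% at a 10% share and 2.5–3% at 20%, while the center model stays near 5%. If centers do not differ at all, the center term costs at most about half a point of power (89.9% against 89.3% with one list).

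These sizes rest on assumed shares, four near-equal centers, blocks of 4 and the article's SD of 3.15. They were worked out for VO2 max only; the article gives no corresponding figures for the walk test or the quality-of-life score.

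The sentence in section 2.1 promises more than randomising 152 patients can deliver. Balance holds in expectation.

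**What to change.** - **Section 2.8.** Make the primary between-group comparison of VO2 max, six-minute walk distance and the Minnesota score a linear model with treatment arm and center as fixed effects, specified in advance. It replaces the unadjusted t-test and the adjustment triggered by observed imbalance. Show the treatment effect by center descriptively, without a test in each center.
- **Section 2.4.** State whether allocation lists are separate by center. Stratifying by center is good practice; if it is already done, say so, and the center term then matches the design. If one list is used, the same model remains valid.
- **Section 2.1.** Reword the claim to say that randomisation balances characteristics between arms in expectation.

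The cost is 3 degrees of freedom and slight extra analysis work. No additional patients, visits or staff are needed.
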